#### **8.5.5 Reporting of SAEs**

If an SAE occurs, the Serious Adverse Event reporting form must be completed.

An SAE must be reported to the principal investigator – medical monitor as soon as possible.

The SAE will also be reported to the Ethics Committee.

### **8.6 Pregnancy and Postpartum Information**

#### **8.6.1 Participants Who Become Pregnant During the Trial**

The participant must inform us of the pregnancy, which will result in exclusion from the study.

Since no adverse effects have been recorded, no follow-up will be provided.

#### **8.6.2 Participants Whose Partners Become Pregnant**

This does not pose any problem for participation.

## 9. Statistical Considerations

### 9.1 Statistical Analysis

Demographic data and baseline values will be used to describe the study groups.

The difference in each parameter compared to baseline will be analyzed using ANCOVA by treatment group, adjusted for baseline values. An  $\alpha$ -level of 0.025 will be applied for the primary analysis. For secondary and exploratory analyses, an  $\alpha$ -level of 0.05 will be used.

The absolute change from baseline in blood pressure over time will be studied using Linear Mixed Models. Baseline value, treatment group, time point, and the interaction between treatment group and time point will be fixed variables. Participant ID will be a random variable.

As sensitivity or exploratory analyses, predictors such as sex, age, baseline values, or compliance may be added to the models to assess whether they have a significant effect.

Subgroup analyses may also be performed, and other continuous parameters can be studied using the same method.

No interim analysis is planned.

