#### 3.2 Endpoints

|                    | Objective                                              | Endpoint                                                                                                                               |
|--------------------|--------------------------------------------------------|----------------------------------------------------------------------------------------------------------------------------------------|
| Primary     | Decrease in blood pressure                             | Systolic blood pressure*                                                                                                               |
| Secondary   | Decrease in blood pressure                             | Systolic blood pressure after 4 weeks*                                                                                                 |
|                    | Decrease in blood pressure                             | Diastolic blood pressure*                                                                                                              |
|                    | Change in markers of oxidative stress                  | oxLDL*, MDA*, GSH*                                                                                                                     |
|                    | Change in lipid profile                                | Total cholesterol*, HDL*, LDL*, non-HDL*, Remnant cholesterol*, Triglycerides*, Apolipoprotein A1*, Apolipoprotein B*, Lipoprotein(a)* |
|                    | Evaluation of side effects                             | Side effects                                                                                                                           |
| Exploratory | Change in parameters linked to metabolic syndrome.     | Fasted glucose*, Hemoglobin A1c*, fasted insulin*, fasted C-peptide*                                                                   |
|                    | Change in parameters linked to metabolic syndrome.     | BMI* en waist circumference*                                                                                                           |
|                    | Change in parameters linked to cardiovascular diseases | Hemoglobin*, Creatinine*, CRP-US*, Homocysteine*                                                                                       |

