\* This always refers to the absolute difference compared to the baseline value after 8–9 weeks, unless stated otherwise.

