### 9.2 Sample Size Determination

Previous studies observed a reduction in systolic blood pressure of  $10.4 \pm 11.4$  mmHg after intake of olive extract [10,11]. A reduction in systolic blood pressure is the primary endpoint and is therefore used to determine the sample size.

Since another study will examine a different primary endpoint in participants from the placebo group of this study, an  $\alpha$ -level of 0.025 is used. The planned power is 80%.

It is calculated that at least 25 participants per group are needed to detect this effect. This calculation was performed using G\*Power 3.1. Considering an anticipated dropout rate of 10%, 28 participants per group (56 in total) will be recruited for this study.

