### 10.3 Data Protection

The identity and participation in this study will be treated with strict confidentiality. The participant will not be identified by name or in any other way in files, results, or publications related to the study. To guarantee privacy, data will be pseudonymized. All further processing will be carried out on these pseudonymized data. The link between the pseudonym and the individual will be retained only to allow certain information to be communicated back to the participant in their own interest.

The participant consents to the use of personal data collected for this study. This consent can be withdrawn at any time. If participation ends prematurely, the original consent allows the use of data collected during the period the participant was actively involved in the study. Only individuals directly involved in the study will have access to personal data. Data will not be shared with third parties. Researchers will retain the data for a period of 25 years.

The participant has the right to ask the researcher which data are collected and for what purpose. The participant may request corrections or deletion of certain data or ask that data no longer be used. All data will be handled in accordance with the “Directive on the protection of individuals regarding the processing of personal data” and applicable national legislation, including the European General Data Protection Regulation (GDPR – EU2016/679) and Belgian law implementing this regulation. Questions regarding data management can be addressed to the study physician or treating physician.

If the participant feels that their rights regarding personal data are not adequately respected, they may contact the Data Protection Officer, who will take appropriate measures. The participant also has the right to file a complaint with the Belgian Data Protection Authority. More information: <https://www.uza.be/privacy.html>.

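### The primary ANCOVA at week 8–9 cannot use the week-4 systolic pressure of someone who leaves after week 4, although a mixed model planned in the same section can

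*Protocol*

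**What the plan says.** **Endpoint.** Protocol section 3.2 makes systolic pressure primary and fixes the time point in a footnote: "This always refers to the absolute difference compared to the baseline value after 8–9 weeks, unless stated otherwise". The secondary endpoints include "Systolic blood pressure after 4 weeks".

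**Primary test.** Section 9.1: "The difference in each parameter compared to baseline will be analyzed using ANCOVA by treatment group, adjusted for baseline values". The next sentence says that a "level of 0.025 will be applied for the primary analysis". The ANCOVA is not labelled primary word for word, but this is the natural reading.

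**Mixed model.** A separate paragraph of section 9.1 adds: "The absolute change from baseline in blood pressure over time will be studied using Linear Mixed Models". Its terms are given: "Baseline value, treatment group, time point, and the interaction between treatment group and time point will be fixed variables", with participant as the random term. It has no primary role and no significance level of its own.

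**Dropout.** Section 9.2: "Considering an anticipated dropout rate of 10%, 28 participants per group (56 in total) will be recruited for this study". Under section 7.1.2, a participant who stops treatment is excluded from the study. Under section 7.3, non-completers are not replaced. Section 10.3 settles that readings taken before leaving may be used: "the original consent allows the use of data collected during the period the participant was actively involved in the study".

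Section 9.1 gives no missing-data rule. The statistical analysis plan is not shown and may contain one.

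**The concern.** Blood pressure is taken at week 4 in everyone still in the study. A participant who leaves after that visit has a baseline and one on-treatment reading, and consent covers their use. A week 8–9 ANCOVA without imputation drops this person from the primary test. A likelihood-based model of both visits keeps the person and uses the week-4 value to inform week 8–9.

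Two things are at stake:

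- **Precision.** Some information already collected does not reach the primary test.
- **Bias.** If those whose pressure has not fallen by week 4 leave more often, and the product works, placebo loses more of its poor responders than active does. The groups that remain then look more alike than the randomised groups. Recruiting 28 instead of 25 per group restores numbers but does not remove this bias.

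A smaller point follows. As written, the mixed model has only a main effect of baseline and a participant random term. Its week 8–9 contrast therefore need not equal the ANCOVA result, so two different week 8–9 estimates could be reported.

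**Working it through.** **1. Reproduce the plan's sample size.** Inputs from section 9.2: difference 10.4 mmHg, SD 11.4, alpha 0.025, power 80%, dropout 10%. The standardised effect is d = 10.4/11.4 = 0.912. In a two-sample t-test with n per group, the noncentrality is d·√(n/2) on 2n − 2 degrees of freedom. The protocol does not state sidedness. Two-sided 0.025 reproduces its figure, while one-sided gives 20 per group.

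- n = 24: power 79.7%.
- n = 25: power 81.6%, so 25 per group, as stated.
- 25/0.9 = 27.8, so 28 per group, as stated.
- No dropout (n = 28): power 86.3%, the ceiling for any recovery of information.

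**2. Gain if dropout is random.** Let r be the week-4/week-8 correlation given baseline. It is not in the documents, and 0.3 to 0.8 is assumed. With 25 completers and n₄ participants per group who have a week-4 reading, the variance of the week-8 mean is proportional to

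(1 − r²)/25 + r²/n₄,

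and the effective n is its reciprocal. If all 3 dropouts per group have a week-4 reading, n₄ = 28:

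- r = 0.3: 0.91/25 + 0.09/28 = 0.03961, effective n 25.2, power 82.0%.
- r = 0.5: 0.75/25 + 0.25/28 = 0.03893, effective n 25.7, power 82.8%.
- r = 0.8: 0.36/25 + 0.64/28 = 0.03726, effective n 26.8, power 84.6%.

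If only half of the dropouts have a week-4 reading, power is 81.8–83.2%. Against 81.6% without week 4, the gain is 0.2 to 3.0 points.

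**3. Bias if dropout depends on response (simulation).** Document inputs: 28 per group, SD 11.4, effect 10.4 mmHg, alpha 0.025 (two-sided as in step 1). Assumptions: about 10% leave overall, r is 0.5 or 0.7, and the chance of leaving is logistic in the observed week-4 change. For the steep case the slope is 1.5 per SD, the effect is 10.4 mmHg at both visits and all dropout falls after week 4. The ranges combine several runs of 4,000 to 6,000 trials per setting.

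| Dropout pattern (assumed) | ANCOVA or completers' contrast | Likelihood model using week 4 |
|---|---|---|
| Random, 10% | 10.4 mmHg, power 80–81% | 10.4 mmHg, power 81–82% |
| One rule on observed change, slope 0.5 | pulled in by about 0.1–0.2 mmHg, power 81–82% | not tabulated |
| One rule on observed change, slope 1.5 | 9.5–9.9 mmHg, power 75–79% | 10.4–10.5 mmHg, power 80–83% |
| Slope 1.5, but only half of dropout after week 4 | about 10.1 mmHg, power about 81% | not tabulated |
| Dependence relative to own-arm mean | no bias beyond simulation error, power held | no bias |

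The steep case implies about 15% dropout on placebo and 5% on active: 0.15 × 28 = 4.2 and 0.05 × 28 = 1.4 participants, together 5.6, which is 10% of 56. Its shift is 10.4 − 9.9 = 0.5 to 10.4 − 9.5 = 0.9 mmHg toward no effect. Type I error was near 2–2.8% for both methods.

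The direction follows from the rule. In an extreme set-up with opposite dependence in the two arms (r = 0.3 to 0.7), the completers' contrast moved 0.8–1.6 mmHg away from zero. Using week 4 removed that shift to within simulation error.

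**The case against.** The case for leaving section 9.1 alone is substantial.

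- **No error or contradiction.** A baseline-adjusted ANCOVA at the endpoint's own time point is standard and valid, and it matches section 3.2. This stands. The point concerns a better use of data already collected.
- **Completers-only handling is inferred.** An unseen statistical analysis plan could impute from week 4. This stands as a condition on the point, though not against naming one primary model in the protocol.
- **Few participants are affected.** The expectation is about three per group, and section 7.3 expects few non-completers. This stands and limits the size.
- **The larger bias needs stacked assumptions.** It needs all dropout after week 4, steep dependence on the observed change and a threefold imbalance between arms. This stands. Without that combination the shift is about 0–0.3 mmHg in the same-rule settings tried.
- **The written mixed model would have to be altered before promotion.** True: it needs an extra term and a freer covariance.

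Two stronger readings are tempting. A reader might infer that the plan throws away the week-4 pressure of every expected dropout. It does not: those who leave before week 4 have no such reading and add nothing to either model, and the protocol does not say when dropout is expected. The other week-4 readings still serve the week-4 secondary endpoint and the mixed model, and are lost only to the primary test. A reader might also infer that the trial falls short of its planned 80% power. Section 9.2 already allows for 10% dropout, and 25 completers per group give 81.6%. Clearly lower power appears only in the steep case.

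**Conclusion.** The point holds as a cheap improvement. On its natural reading, section 9.1 makes a week 8–9 ANCOVA the primary test. Without imputation, that test ignores the week-4 reading of anyone who leaves later, while a model planned beside it would use that reading.

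Under random dropout the benefit is only 0 to 3 points of power. The better reason to act is protection against dropout related to the week-4 response, where the ANCOVA estimate may be low by 0.1–0.2 mmHg (weak dependence) to 0.5–0.9 mmHg (steep dependence), out of 10.4 mmHg. These sizes rest on assumed dropout timing, assumed dependence and an assumed week-4/week-8 correlation. The protocol supports none of these directly, and it does not show that such dropout will occur. The protection also relies on data being missing at random given baseline, treatment and the week-4 reading.

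**What to change.** In section 9.1, name one primary analysis of systolic pressure: the week 8–9 treatment contrast from the linear mixed model, at alpha 0.025.

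- Include all randomised participants with a baseline and at least one later reading.
- Add a baseline-by-time term to the planned fixed effects.
- Use an unstructured 2×2 covariance for the two visits in place of the random participant term alone.
- Keep the week 8–9 ANCOVA as the sensitivity analysis.

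With these terms each visit has its own intercept, treatment effect and baseline slope. The week 8–9 estimate then equals the ANCOVA estimate when no final visit is missing.

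The cost is about two sentences. No new data are needed, and the endpoint, alpha and sample size do not change. The downside is slightly more modelling and reliance on a missing-at-random assumption, which should be stated.

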## 4. Trial Design

### 4.1 Description of Trial Design

This is a randomised, placebo-controlled, double-blind study. It includes 56 participants, equally divided into 2 groups (28 participants per group). One group will receive Tensiofytol®, and the other will receive a placebo.

Participation in this study will take a maximum of 10 weeks. The potential participant will be invited for a screening visit. If eligible, the participant will be randomised. The study product will then be delivered to the participant as soon as possible. Intake of the study product must start no later than 1 week after the screening visit. The participant must then take the study product or placebo daily. An interim blood pressure measurement will take place 4 weeks after starting intake. The final visit will be scheduled 8 to a maximum of 9 weeks after starting intake. After the final visit, the participant will be unblinded, marking the end of participation.

Participants will be stratified by sex and then randomised into 2 groups. This will occur 1 to 2 days after the screening visit, once all results are available.

This study is double-blind. The investigators do not know which group the participant is assigned to. The participant will be informed of the treatment they received during the final visit, after all data have been collected. The randomisation list and unblinding at the final visit will be handled by a separate study staff member responsible solely for these tasks.

This is a single-centre study. Participants will be enrolled by researchers from the NatuRAPT research group.

Statistical analysis will be performed after all data from all participants have been collected. No interim analysis is planned.

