## 6.6 Participant Assignment, Randomisation and Blinding

### 6.6.1 Participant Assignment

Participants will be stratified by sex and randomised after collecting and reviewing the inclusion criteria.

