### 6.6.2 Randomisation

Participant numbers will be stratified into two groups by sex and then randomised using an online tool (“Clinical Trial Randomization Tool.” The National Cancer Institute's Division of Cancer Prevention, <https://ctrandomization.cancer.gov>), resulting in two lists of numbers. The aim is to include an equal number of men and women in each group.

Participants will be assigned to these lists in the order of inclusion and thus randomised accordingly.

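### Randomisation is stratified by sex, but the primary ANCOVA and the mixed model leave sex out, so the test may be slightly conservative (low severity)

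*Protocol*

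**What the plan says.** Sex is the only stratification factor. Section 4.1 states: "Participants will be stratified by sex and then randomised into 2 groups". Section 6.6.1 repeats it: "Participants will be stratified by sex and randomised after collecting and reviewing the inclusion criteria". Section 6.6.2 describes separate randomisation lists for the two sexes and gives the purpose: "The aim is to include an equal number of men and women in each group".

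Section 9.1 then fixes the models. For the ANCOVA: "The difference in each parameter compared to baseline will be analyzed using ANCOVA by treatment group, adjusted for baseline values". For the mixed model: "Baseline value, treatment group, time point, and the interaction between treatment group and time point will be fixed variables", with participant as the random term. Sex enters only through the sentence "As sensitivity or exploratory analyses, predictors such as sex, age, baseline values, or compliance may be added to the models", and the stated reason for adding such predictors is to see whether they are significant.

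The SAP is not at hand. However, section 9.1 does not leave the question open. It names the ANCOVA covariate, lists the mixed-model terms and gives sex an optional role, so an SAP with sex in the main models would depart from the protocol.

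**The concern.** Balancing the arms on sex removes the difference between men and women from the treatment contrast. A model without sex still counts that difference as residual noise. If sex is prognostic for the change in blood pressure after baseline adjustment, the reported standard error then exceeds the real variability of the estimate. The confidence interval is too wide, the test rejects less often than its nominal level, and the precision gained by stratifying is not used. In a trial of 28 per arm even a modest loss is worth avoiding if it is cheap to do so.

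A smaller issue is that the optional wording makes the use of sex depend on its p-value. A stratification factor belongs in the model because of the design. As written, the text permits two versions of the treatment comparison, with and without sex, with nothing fixed in advance about which is reported.

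**Working it through.** **Inputs from the protocol (sections 9.1 and 9.2).** Effect 10.4 mmHg, SD 11.4 mmHg, power 80%, 25 evaluable per group, 10% dropout, 28 per group recruited. For alpha, 9.1 says "level of 0.025 will be applied for the primary analysis" and 9.2 says "level of 0.025 is used". Sidedness is not stated.

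**Step 1: reproduce the plan's sample size.** Two-sample t-test with noncentral t and d = 10.4 / 11.4 = 0.912:
- two-sided 0.025: 25 per group, power 81.6%
- one-sided 0.025: 20 per group
- two-sided 0.05: 20 per group
- one-sided 0.05: 16 per group

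Only two-sided 0.025 gives the stated 25, so that reading is used below. Dropout: 25 / 0.9 = 27.8, rounded up to 28.

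**Step 2: effect on the standard error.** Let D be the difference between men and women in change, after baseline adjustment. D is an assumption, since the documents give no value. Keep the total SD at 11.4 and take equal numbers of men and women in each arm. The variance due to sex is D²/4, the within-sex SD is √(11.4² − D²/4), and the standard error is SD × √(2/28) = SD × 0.267.

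| D (mmHg) | Share of variance due to sex | Within-sex SD | SE, sex omitted | SE, sex in model |
|---|---|---|---|---|
| 0 | 0 | 11.40 | 3.05 | 3.05 |
| 5 | 6.25 / 129.96 = 4.8% | 11.12 | 3.05 | 2.97 |
| 8 | 16 / 129.96 = 12.3% | 10.68 | 3.05 | 2.85 |

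With balanced arms, the last column is also about the true variability of the estimate when sex is omitted.

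**Step 3: type I error without sex.** Normal approximation, critical value 2.241 for two-sided 0.025:
- D = 5: 2.241 × 3.05 / 2.97 = 2.30, two-sided tail about 2.2%
- D = 8: 2.241 × 3.05 / 2.85 = 2.40, two-sided tail about 1.6 to 1.7%

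Simulation of the baseline-adjusted ANCOVA gives about 2.1% and 1.6%.

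**Step 4: power at 28 per arm.** Simulated baseline-adjusted ANCOVA, effect 10.4 mmHg:

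| D (mmHg) | Power, sex omitted | Power, sex in model |
|---|---|---|
| 0 | 85.2% | 85.1% |
| 5 | 86.0% | 87.1% |
| 8 | 86.4% | 89.4% |

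**Step 5: the same at 25 per arm**, the number left after the planned dropout, by assumed share of residual variance due to sex (40,000 simulated trials per cell):

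| Share | Power, sex omitted | Power, sex in model | Type I error, sex omitted |
|---|---|---|---|
| 0% | 80.9% | 80.8% | 0.025 |
| 2% | 80.9% | 81.5% | 0.024 |
| 5% | 81.2% | 82.8% | 0.022 |
| 10% | 81.4% | 84.6% | 0.018 |
| 20% | 82.6% | 88.9% | 0.014 |

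With sex in the model, type I error stays at about 0.025. The 20% row corresponds to a sex difference of 10.2 mmHg, nearly the whole planned treatment effect, and is shown only as an extreme.

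**The case against.** The strongest reply is that little is lost. The size of the problem depends on the sex difference in change after baseline adjustment, which no document gives. Any sex difference that runs through baseline blood pressure is already partly absorbed by the baseline term. If the remaining difference is small, so is the loss: at a 2% share of variance it is about half a point of power. This stands, and it is why the severity is low.

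The conservatism also needs the arms to be balanced within sex. Section 6.6.2 gives equal numbers as an aim and states no block size, and section 7.3 says participants who do not complete will not be replaced. If allocation within sex were unrestricted, the standard error without sex would be about right on average and type I error close to nominal. This stands as a condition on the claim, although balance is what the protocol says it wants.

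Section 9.1 does foresee a sex-adjusted result as a sensitivity analysis. That lessens the point without removing it, because the analysis is optional and the primary test remains the one without sex.

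A reader might go further and infer that the trial is underpowered, that its false-positive risk is raised or that its estimate is biased. The documents support none of these. Balanced omission of a covariate from a linear model does not bias the treatment estimate, the error is in the conservative direction, and power without sex is at or above 80% in every case above. Larger losses appear only with other inputs. An effect of 8 mmHg, a within-sex SD of 9.9 and a sex difference of 8 mmHg, for example, give about 70% against 76%. The effect and the SD there are not the protocol's planning values, and the sex difference is added on top of the SD.

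**Conclusion.** The inconsistency is real: the protocol randomises by sex, and section 9.1 keeps sex out of the models that carry the conclusions. The consequence is minor and conditional. With the protocol's planning values at 28 per arm and assumed sex differences in change of 0 to 8 mmHg, type I error falls from 2.5% to as low as about 1.6%, and about 0 to 3 points of power are lost. If sex does not predict change after baseline adjustment, nothing is lost.

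This rests on alpha being two-sided (the only reading that reproduces 25 per group), on a total residual SD of 11.4, on the lists achieving balance within sex, and on a sex effect whose size is unknown. The stated sample size is not called into question. The same reasoning applies to the mixed model and the secondary ANCOVAs, but no size was computed for those. Low severity.

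**What to change.** In section 9.1, define the primary model as change in systolic blood pressure = treatment + baseline systolic blood pressure + sex. Add sex as a fixed effect to the mixed model and to the ANCOVAs of the secondary endpoints. Remove sex from the list of optional predictors. That list also names baseline values, which are already in both models, and can be tidied in the same edit. Age and compliance can stay as sensitivity or exploratory terms.

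The cost is a sentence or two of text and one degree of freedom. If sex turns out not to matter, the price is about a tenth of a point of power (80.9% against 80.8% at 25 per arm). No change to the sample size is needed.

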### **Study Design**

Randomised, placebo-controlled, double-blind study investigating the effect, tolerance, and efficacy of Tensiofytol® compared to a placebo in individuals aged 18 years or older and younger than 78 years with elevated blood pressure.

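### The primary model adjusts only for the baseline value; sex and age are optional extras judged by their own significance, which may forgo some precision and does not check the treatment effect

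*Protocol*

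**What the plan says.** Section 9.1 states that the change from baseline in each parameter "will be analyzed using ANCOVA by treatment group, adjusted for baseline values". The linear mixed model for blood pressure has baseline value, treatment group, time point and the treatment-by-time interaction as fixed effects, and participant as a random effect. Neither model contains sex or age.

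The next paragraph deals with other predictors. It opens "As sensitivity or exploratory analyses" and continues: "predictors such as sex, age, baseline values, or compliance may be added to the models to assess whether they have a significant effect". The wording is permissive: it requires no model and gives its list as examples.

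Two of the listed predictors are fixed before allocation. Age is an eligibility item, since the synopsis (Study Design) enrols "individuals aged 18 years or older and younger than 78 years". Sex is the stratifier: section 4.1 says "Participants will be stratified by sex and then randomised into 2 groups". Compliance is different. Under section 6.7 it comes from a capsule count at the end of the study. The baseline value is also on the list, although it is already in both models.

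**The concern.** There are two separate issues.

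**Choice of covariates.** A baseline variable that predicts the change in systolic pressure reduces the residual variance if it is named in advance, and costs one degree of freedom if it does not predict. Sex has the stronger claim, because randomisation is stratified on it and the analysis would then follow the design. Age is not balanced by design and spans 18 to 77 years. In a trial planned at 25 evaluable participants per group, either could narrow the interval for the primary comparison.

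**Purpose of the sensitivity models.** A sensitivity analysis should ask whether the treatment difference holds under another reasonable model. Section 9.1 asks whether the added predictor is significant. A predictor can miss significance in about 50 people and still move the treatment estimate through chance imbalance. A strongly significant predictor that is balanced between arms leaves the estimate almost unchanged. Neither result tells the reader how stable the blood pressure finding is.

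**Working it through.** **Inputs.** From section 9.2: effect 10.4 mmHg, SD 11.4 mmHg, planned power 80%, at least 25 per group, 28 with 10% dropout, and for alpha "level of 0.025 is used" (0.025). The section does not say whether the test is one- or two-sided. The partial correlation r of age with the change, given treatment and baseline, is not in the protocol. It is an assumption here, shown as a range.

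**Step 1: the plan's own figure.** Two-sample t-test, noncentral t, standardised effect 10.4/11.4 = 0.912.
- Two-sided alpha 0.025: 25 per group, power 81.6%. This matches the plan.
- One-sided 0.025, or two-sided 0.05: 20 per group. This does not match, so two-sided 0.025 is used below.
- Dropout: 25/0.90 = 27.8, rounded up to 28, as stated.

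**Step 2: power with the baseline value only.** Take 11.4 as the residual SD after baseline adjustment. The standard error of the treatment difference is 11.4 × sqrt(2/25) = 3.22 mmHg and the noncentrality is 10.4/3.22 = 3.23. With 50 − 3 = 47 error degrees of freedom, power is 81.5%. The half-width of the 97.5% interval is 7.47 mmHg.

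**Step 3: power with age added.** The residual SD becomes 11.4 × sqrt(1 − r²), with 46 degrees of freedom.

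| Assumed r | Residual SD (mmHg) | Power |
|---|---|---|
| 0 | 11.40 | 81.5% |
| 0.1 | 11.34 | 81.9% |
| 0.2 | 11.17 | 83.1% |
| 0.3 | 10.87 | 85.2% |
| 0.4 | 10.45 | 88.1% |

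If age predicts nothing, the loss is 81.52% − 81.47% = 0.05 point. If sex is added as well and also predicts nothing, the degrees of freedom fall to 45 and power is 81.41%, a total loss of about 0.1 point. At r² = 0.05 (r about 0.22) the interval half-width falls from 7.47 to 7.28 mmHg.

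**Step 4: what the covariate's p-value shows.** Test of age at 0.05 on 46 degrees of freedom, with noncentrality r/sqrt(1 − r²) × sqrt(50). The shift in the treatment estimate from an age imbalance of one standard error is r × 11.4 × sqrt(2/25).

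| Assumed r | Noncentrality | Age reaches p < 0.05 | Shift at 1 SE of imbalance | Shift at 2 SE |
|---|---|---|---|---|
| 0.2 | 1.44 | 29% | 0.64 mmHg | 1.3 mmHg |
| 0.3 | 2.22 | 59% | 0.97 mmHg | 1.9 mmHg |

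For scale, against the standard error of 3.22 mmHg these shifts run from 0.64/3.22 = 0.2 to 1.9/3.22 = 0.6 of a standard error. So at r = 0.2 age would be called non-significant about 71% of the time, whether or not it had moved the estimate.

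**The case against.** The other side has a good case on several points.

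- **No bias.** A reader might infer that leaving age out distorts the result. It does not: in a randomised comparison with a linear model, omitting a baseline covariate leaves the treatment effect unbiased. Age is not a stratification factor, and nothing in the protocol calls it prognostic for the change. This stands.
- **No demonstrated loss.** A reader might also infer that precision is lost for certain, or that the trial is underpowered. The documents support neither. The gain depends on a correlation they do not give, it is at most 1.6 points (83.1 − 81.5) for r up to 0.2, and 80% power is reached without age. This stands, and limits the claim to precision that may be forgone.
- **The imbalance shifts are modest.** The larger ones need a two-standard-error imbalance, which happens by chance in about 5% of trials, and the reported interval already allows for chance imbalance. This stands. The shifts show that the significance criterion is uninformative, not that the primary result is unsafe.
- **No selection rule.** It is tempting to read section 9.1 as letting significant predictors into the primary model. It does not say so. The primary ANCOVA is fixed separately and the added models are labelled sensitivity or exploratory.
- **Robustness is not ignored.** Any extended model yields an adjusted treatment estimate, so it would be too strong to say that robustness goes untested. A statistical analysis plan, not shown, may set out the models and their reporting. The wording is also a machine translation from Dutch.

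The last point does not remove the fault in purpose. Details of sensitivity models may be left to an analysis plan, but the protocol itself states what these models are for, and that purpose does not address the treatment effect.

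**Conclusion.** The point holds as a minor improvement. Section 9.1 leaves sex and age, both known before randomisation, out of the primary ANCOVA and the mixed model, and gives the optional models that include them a purpose that cannot show whether the treatment effect is robust.

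The possible gain from age is 0 to 1.6 power points for a partial correlation of 0 to 0.2, and 3.7 points (85.2 − 81.5) at 0.3. The worst-case loss is about 0.05 point for age alone, or about 0.1 point for sex and age together. These figures assume 25 evaluable per group, a residual SD of 11.4 mmHg after baseline adjustment and two-sided alpha 0.025. The protocol gives no correlation for age or sex, so the gain could be nil. The case for sex rests on its role as stratifier, not on a calculated gain.

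**What to change.** 1. Pre-specify sex (as stratification factor) and age (continuous), with the baseline value, as covariates in the primary ANCOVA and in the blood pressure mixed model.
2. Replace the clause about assessing whether predictors are significant with a reporting rule: give the treatment difference and its confidence interval (97.5% for the primary endpoint) from each extended or reduced model beside the primary estimate, whatever the covariate's p-value. The baseline-only model then serves as one of the reduced models.
3. Take compliance out of this list of baseline covariates, because it is measured after randomisation. Drop the baseline value from the list too, as it is already in both models.

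The cost is a few lines in section 9.1, or in an analysis plan together with a corrected protocol sentence, and one degree of freedom per added covariate out of 47. No new data and no change in sample size are needed.
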